### Assessment of gut microbiota

Fecal samples will be obtained daily for 3 days at baseline and at the final 3 days of the intervention (after 6 months) in sterile plastic containers and delivered to the Infectious Diseases and Tropical Medicine Research Center Laboratory within 4 hours of collection. After being given a code, samples will be immediately frozen at −80 °C until final processing. DNA will be extracted from fecal samples (from the 3 composite days mixed equally) using DNA Extraction Stool Mini Kit (Qiagen, Hilden, Germany) according to the manufacturer’s instructions. Numbers of phylum Firmicutes and Bacteroidets will be determined by quantitative real-time polymerase chain reactions (qPCR) methodology using specific designed primers and Taqman probes.

The composition and ratio of the two fecal bacteria before and after supplementation with probiotics, synbiotics, and placebo will be compared.

## Data analysis

### Sample size

Calculation of sample size was based on a parallel three-group randomized clinical trial with repeated measurements of main outcomes at three time points. Considering a type one error rate of $$ \upalpha =0.05 $$, and statistical power of 1 − β = 0.80 (^*Z*^
_1 − *β*_ = 0.84) for detecting a standardized effect size of at least Δ = 0.60 in order to have the largest number of participants in a repeated measures design structure based on the following formula, 29 subjects were determined. Compensating for possible attrition, 30% additional samples will be recruited, in which a final 40 subjects in each study group will participate.$$ R=\left[\frac{1+\left( w-1\right)\;\rho}{w}-\frac{v{\rho}^2}{1+\left( v-1\right)\rho}\right];{n_{1\;}}_{repeated}= R\left[\frac{2{\left({z}_{1-\alpha /2}+{z}_{1-\beta}\right)}^2}{\varDelta^2}+\frac{z_{{}_{1-\alpha /2}}^2}{4}\right] $$

In this formula, Δ is the standardized effect size, R will be determined based on number of observations before intervention, v (in our study v = 1), number of observation after intervention, w (in the current study w = 2) and intracluster correlation coefficient ρ, that was considered as ρ = 0.7 [27].

The participant’s adhesion and retention will be managed by the project coordinator who will conduct weekly contact. We anticipate that it will take 12 months to recruit this sample size. All of the outcome data will be collected even for participants who discontinue or deviate from intervention protocols.

### Randomization

A computer-generated list of random numbers is used to create a series of sequentially numbered envelopes containing equal assignments to either placebo, probiotic or symbiotic. The study epidemiologist is responsible for the randomization and the study pharmacist for delivery of the blinded supplements. The supplements, which will be assigned letter A, B or C, are otherwise identical and the participants, investigators, outcome assessors, and data analysts will be blinded after assignment to interventions.

### Statistical analysis

Record data including outcome data and adverse events will be double-entered on SPSS software (Version [15], SPSS Inc., Chicago, IL, USA) to secure its validity. Descriptive univariate analyses on all study variables through presenting them as mean ± standard deviation (SD) (for normally distributed continuous) or median [interquartile range (IQR)] for nonnormal quantitative data and frequency (percentage) for categorical data will be conducted. Data will be evaluated for the presence of outliers, violations of normality, and missing data. Major violations of normality will be corrected with an appropriate transformation procedure, i.e., logarithmic transformation for positively skewed and exponential function for negatively skewed data. In the case of an outlier, rather than transform the data, the outlier will be “Winsorized,” that is, replaced by the most extreme value in the tail of the distribution as well as a sensitivity analysis being performed when outliers are in or out of analyses. To test our hypothesis that probiotic and synbiotic supplementations will improve main outcomes in prediabetic participants, a repeated measures analysis of variance (ANOVA) with a between-subject factors approach will be used. The multiple observations will be considered as nested data within individuals. This will allow us to make inference about time effects (i.e., comparison between the time points while accounting for the correlation in the data) in each studied treatment group and to make inference about differences between competing treatment groups. This approach enables us to make an inference regarding the group by time interaction as a primary important interested component. As a perquisite, the assumption of sphericity will be evaluated using a Muchly test, in the case of violation, multivariate or Huynh-Feldt approaches will be employed. A compound symmetry error structure will be chosen for this model when the assumption is present. We will use repeated measures ANOVA as the main approach for testing all our hypothesis regarding the main outcomes; simultaneously, independent *t* test along with Bonferroni adjustment will be conducted for comparing outcomes in each follow-up time point between study groups. Some prespecified subgroup analysis will be done based on some confounding variables such as age, gender, etc., for detecting significant differences in intervention efficacy across the strata of mentioned variables. However, these subsamples will be compared to the main dependent variables at baseline. If the groups are found to be different from one another then they will be entered into the model as a covariate. On the other hand, the baseline values of the main dependent variables and other potential confounding variables will be considered as covariates and they will be adjusted in all fitted models. The study analyst will have access to the results and final trial dataset and make the final decision on interim analyses and terminate the trial if there is any harm for the participants.

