### The specific aims and hypotheses

#### Aim 1

To determine whether probiotic or synbiotic supplementation improves fasting plasma glucose, insulin resistance (primary outcome), and beta-cell function in individuals at elevated risk of developing T2DM. We hypothesize that probiotic and synbiotic supplementation will improve fasting plasma glucose, insulin sensitivity, and beta-cell function in these individuals compared with placebo.

#### Aim 2

To determine whether probiotic or synbiotic supplementation will improve lipid profiles in individuals at elevated risk of developing T2DM. We hypothesize that probiotic and synbiotic supplementation will reduce serum triglyceride and non-high-density lipoprotein (HDL) cholesterol, elevate HDL cholesterol, and improve low-density lipoprotein (LDL)/HDL, total cholesterol (TC)/HDL and triglyceride (TG)/HDL in these individuals.

#### Aim 3

To determine whether probiotic or synbiotic supplementation will improve anthropometric indicators in individuals at elevated risk of developing T2DM. We hypothesize that probiotic and synbiotic supplementation will improve body mass index (BMI), waist circumference and waist-to-hip ratio (WHR) in these individuals.

#### Aim 4

To determine the changes in abundance and ratio of two dominant groups of gut microbiota including Firmicutes and Bacteroidetes and their relation with metabolic syndrome indices during supplementation. We hypothesize that the change in Gram-positive gut microbiota (Firmicutes) and Firmicutes-to-Bacteroidetes ratio with probiotic and synbiotic supplementation will be correlated with the change observed in the metabolic variables.

#### Aim 5

To compare the effects of probiotic and synbiotic supplements on gut microbiota, anthropometric, glycemic, and lipid profiles. We hypothesize that synbiotic supplements will have more efficacy to improve these indicators than probiotic.

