### Anthropometric parameters and blood pressure measurement

Height, weight, waist and hip circumferences will be measured at baseline and will be repeated at months 3, 6, 12, and 18.

Height will be determined using a scale-mounted stadiometer to the nearest 0.5 cm and weight will be measured with light clothing to the nearest 0.1 kg. BMI will be calculated by dividing each participant’s weight in kilograms by height in meters squared. Waist circumference will be measured at the midpoint between the lowest rib and the iliac crest to the nearest 0.1 cm using a flexible tape. Hip circumference will be measured around the widest portion of the buttocks by the tape. The waist-to-hip ratio (WHR) will be calculated according to World Health Organization (WHO) recommendations [23]. All the measurements will be taken by one person to decrease the error rate.

Blood pressure for each participant will be measured by a trained nurse on two occasions using a mercury sphygmomanometer in both of the hands and the mean blood pressure readings will be used for the analysis according to American Heart Association guidelines [24]. Participants will be instructed to rest for 10 minutes prior to the first blood pressure measurement with a minimum of 15 minutes between the two occasions.

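### The exponential transformation prescribed for negatively skewed outcomes makes tests depend on the measurement unit and can worsen non-normality; a minor correction that probably touches secondary outcomes only

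*Protocol article*

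**What the plan says.** The Statistical analysis section of the protocol states: "Major violations of normality will be corrected with an appropriate transformation procedure". It then names two rules after the abbreviation i.e.: "logarithmic transformation for positively skewed and exponential function for negatively skewed data". It gives no rescaling, reflection or unit, and no threshold for a major violation. Outliers have a separate rule: "In the case of an outlier, rather than transform the data, the outlier will be “Winsorized", together with a sensitivity analysis with outliers in and out. The term outlier is not defined.

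The data then go into the planned model: "We will use repeated measures ANOVA as the main approach for testing all our hypothesis regarding the main outcomes". Bonferroni-adjusted t tests are added at each follow-up, and baseline values serve as covariates in all fitted models.

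On scale, the anthropometric section says: "Waist circumference will be measured at the midpoint between the lowest rib and the iliac crest to the nearest 0.1 cm using a flexible tape". Weight is recorded in kg, and blood pressure with a mercury device, which implies mmHg. Aim 2 expects that "probiotic and synbiotic supplementation will reduce serum triglyceride and non-high-density lipoprotein (HDL) cholesterol, elevate HDL cholesterol", but no lipid unit is printed. Glucose appears on a 100–125 scale in Table 1 (mg/dL implied) and in mmol in the HOMA-IR formula.

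**The concern.** A transformation for skewness should bring the data closer to normal and should not let the choice of unit decide the result. The log meets the second condition: a change of unit adds a constant to every log value and leaves the tests unchanged. The exponential does not: multiplying x by c turns exp(x) into its c-th power, which is a different shape.

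At stake is the analysis of any outcome flagged as negatively skewed. On a scale with a large SD, the comparison between arms can become a comparison of the few highest values, and a real effect can be hidden. On a scale with a very small SD, the step does almost nothing.

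**Working it through.** The plan states no figure on this point, so there is none to reproduce.

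**Inputs from the Sample size section:** standardized effect 0.60, correlation 0.7, 40 per group, two-sided alpha 0.05. **Assumed, because the documents give none:** SDs, skewness, and a reflected-gamma shape for negative skew.

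**1. Algebra.** Two waists of 100 and 110 cm differ after transformation by a factor exp(110)/exp(100) = e^10 = 22,026. In inches the same gap is 10/2.54 = 3.94, and the factor is e^3.94, about 51. In metres it is e^0.1, about 1.1.

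**2. Unit dependence of the p-value.** In one simulated waist data set (mean 100 cm, SD 10, 40 per group), the untransformed p-value is 0.0011 in every unit. After exp(x) it is 0.097 in cm, 0.0082 in inches, 0.0002 in decimetres and 0.0007 in metres. For fasting glucose, with an assumed SD of 8 mg/dL and skewness -1.0, baseline-adjusted power is 95% untransformed. After exp(x) it is 20% in mg/dL and 99% in mmol/L.

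**3. Effect by SD.** Unadjusted two-group t test, skewness -1.0, 10,000 runs, power 0.75 untransformed:

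| SD in outcome units | Power after exp(x) | Share of total held by two of 80 participants (median) | Skewness after exp(x) |
|---|---|---|---|
| 0.5 | 0.87 | 5% | +0.5 |
| 1 | 0.92 | 9% | +1.4 |
| 2 | 0.92 | 21% | +3.0 |
| 5 | 0.47 | 57% | +5.8 |
| 10 | 0.08 | 87% | +7.6 |
| 15 | 0.02 | 96% | +8.4 |

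For waist-to-hip ratio (values near 0.9), exp(x) is almost a straight line. Sample skewness moves only from about -0.75 to -0.57, and no power is lost.

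**4. Baseline-adjusted comparison at one visit** (post = pre + group, 40 per arm, 0.6 SD, no Winsorizing):

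- SD 10, skewness -1.0: 95% to 12%; sample skewness from about -0.8 to +7.7.
- SD 10, skewness -1.5: about 94% to 54%.
- SD 10, skewness -2.0: 93% to 97–98%, so no loss.
- Diastolic pressure, SD 8, skewness -1.0: 95% to 20%. BMI, SD 4: 95% to 75%.

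A separate simulation of the planned group-by-time test (three groups, three times, skewness -1.0) gave 0.97 untransformed and 0.06 at SD 10. At SD 2 it gave 0.82 when the effect lowered the outcome and no loss when it raised it. Its own baseline-adjusted comparison fell from 0.99 to 0.18 at SD 10.

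**5. Winsorizing** (SD 10, skewness -1.0, baseline-adjusted; cutoffs assumed). Applied before exp(x), power stays at about 12%, because the outliers lie in the low tail while exp(x) inflates the ordinary high values. Applied after exp(x), power is 88–89% with 1.5-IQR fences, 90% with 3-IQR fences and 57% with a 3-SD rule. At skewness -1.5 the three cutoffs give 98%, 99% and 93%, against 94% untransformed.

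**6. Type I error.** Under the null at SD 10, the t test after exp(x) rejects 0.7% of the time. The test is conservative, not inflated.

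**The case against.** The strongest reply is that the large losses leave out the rest of the plan. Winsorizing after transformation removes most of the loss under two of the three cutoffs tried. Only major violations trigger the rule: at population skewness -1.0, just 34% of simulated samples of 80 had skewness below -1. The loss also shrinks as skew deepens, partly because the assumed reflected gamma has a hard upper bound. All of this stands as a limit on size. It does not rescue the rule, since the plan fixes neither an outlier definition nor the order of the two steps.

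It can also be said that "Major violations of normality will be corrected with an appropriate transformation procedure" leaves room for judgement, that the functions listed are illustrations, or that a power transform such as squaring was meant. The text nevertheless names the exponential function, and if something else was intended the same phrase needs correcting.

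A reader might infer that most outcomes in Aims 2 and 3 are damaged. The documents do not support that. Those aims name nine outcomes: triglyceride, non-HDL, HDL, three lipid ratios, BMI, waist and waist-to-hip ratio. Four are unitless ratios. The three lipid concentrations depend on an unprinted unit; HDL with an assumed SD of 10 mg/dL falls from 94% to 10%, while the same HDL in mmol/L goes from 96% to 98%. Nothing shows that any outcome will be negatively skewed.

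**Conclusion.** The exponential rule is wrong as written: its result depends on the unit, and it does not reliably restore normality. That conclusion follows from the algebra and needs no assumption. The power loss is conditional. At SD 10 and 40 per arm, a baseline-adjusted comparison falls from about 95% to 12% at skewness -1.0, to about 54% at -1.5, and hardly at all at -2.0. With Winsorizing after transformation the range at -1.0 is about 57% to 90%. Outcomes with an SD of about 2 units or less lose little or no power.

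A reader might take the fall to 12% as the expected loss, or infer a threat to the primary result or a risk of false positives. None of these is supported. The figure is a worst case on assumed inputs, HOMA-IR is probably positively skewed and would take the log branch (also an assumption), and the null rejection rate is below 5%. The point is minor because it affects only secondary outcomes that are flagged as negatively skewed.

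**What to change.** In the Statistical analysis section, delete the second half of "logarithmic transformation for positively skewed and exponential function for negatively skewed data" and keep the log for positive skew. Add: *Negatively skewed outcomes will be analysed untransformed in the baseline-adjusted model, with a reflect-and-log analysis as sensitivity; normality will be judged on model residuals.* Tie the reflection constant to the spread of the data. A fixed number such as the maximum plus 1 would bring the unit dependence back.

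In the t-test simulation at skewness -1.0, the untransformed analysis had power 0.75 and reflect-and-log 0.85, so the change gives nothing up there. Robust standard errors or a rank-based analysis are optional.

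The cost is one sentence and one extra sensitivity model per affected outcome, with no new data or participants. The reflect-and-log result is less directly interpretable, which is why it should stay a sensitivity analysis.

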### Biochemical assays

Participants who have met the inclusion criteria (Table 1) will be instructed to arrive at Isfahan Endocrine and Metabolism Research Center for laboratory testing between 7:00 and 9:00 am after a 12-hour overnight fast and not to do vigorous physical activity for the previous 48 hours. Each participant will be tested for the biochemical parameters at baseline and during each follow-up visit (3, 6, 12, and 18 months).

An oral glucose tolerance test (OGTT) will be performed to clarify glycemic status. Plasma lipid and lipoprotein concentrations (i.e., total cholesterol, high- and low-density lipoprotein cholesterol, and triglycerides) will be measured using a photometric assay kit (Pars Azmoon Co., Tehran, Iran). Fasting glucose levels will be measured using the glucose oxidase (GOD) method. Fasting insulin levels will be measured using chemiluminescence (Siemens, Munich, Germany). Ion exchange chromatography will be used to test glycosylated hemoglobin (HbA1c).

The homeostatic model assessment of insulin resistance (HOMA-IR) and homeostatic model assessment of beta-cell function (HOMA-B) index will be used to determine insulin resistance (primary outcome) and beta-cell function respectively using the following formula:$$ \mathrm{HOMA}\hbox{-} \mathrm{I}\mathrm{R}=\mathrm{fasting}\;\mathrm{blood}\;\mathrm{glucose}\;\left(\mathrm{mmol}/\mathrm{ml}\right)\times \mathrm{insulin}\;\mathrm{assay}\;\left(\mathrm{microunit}/\mathrm{ml}\right)/22.5 $$
$$ \upbeta \kern0.5em \mathrm{cell}\kern0.5em \mathrm{function}\kern0.5em \left(\mathrm{HOMA}\hbox{-} \mathrm{B}\right)=\left[\mathrm{fasting}\ \mathrm{insulin} \times 20\right]/\left[\mathrm{fasting}\ \mathrm{glucose}\hbox{-} 3.5\right] $$

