
### Treatment of missing data

Missing data are common in longitudinal studies. Based on patterns and the mechanism of missing data, an appropriate multiple imputation approach will be followed for completing missing data. We will use an intention-to-treat analysis as our primary analytic approach. As an alternative statistical analysis method using linear mixed model ANOVAs or generalized estimating equation (GEE) for longitudinal analysis, we will compare main study outcomes across the treatment groups. Through employing these methods, the possibility for using all available data to construct weighted averages across the different patterns of missing data to provide valid point estimates, and confidence intervals for population parameters will be provided [28]. As a secondary analysis, we will conduct a per protocol analysis and restrict the analyses to only those individuals who complete the intervention; if the results differ we will interpret the findings based on the intention-to-treat analysis.

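### The group-by-time interaction, named as a primary component beside baseline adjustment, is not the active-versus-placebo difference the trial was sized for and, on the ordinary reading, can miss a sustained benefit

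*Protocol article*

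**What the plan says.** All of this is in the protocol article.

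- **Statistical analysis.** Repeated measures ANOVA is the main approach for all hypotheses on the main outcomes. On what is tested: "This approach enables us to make an inference regarding the group by time interaction as a primary important interested component". On adjustment: "the baseline values of the main dependent variables and other potential confounding variables will be considered as covariates", and this applies to all fitted models. The section also mentions inference on differences between treatment groups, and Bonferroni-adjusted t tests between groups at each follow-up visit. It does not list the visits in the model or say whether baseline is a level of the time factor.
- **Sample size.** The calculation assumes "repeated measurements of main outcomes at three time points", one before the intervention (v = 1) and two after (w = 2), with a two-group formula, standardized difference 0.60, correlation 0.7, two-sided alpha 0.05 and "statistical power of 1 − β = 0.80".
- **Biochemical assays.** Outcomes are measured at baseline and "during each follow-up visit (3, 6, 12, and 18 months"). Supplementation lasts 6 months, so months 12 and 18 are off supplement.
- **Aim 1.** The hypothesis is an improvement with probiotic and with synbiotic compared with placebo. Insulin resistance is the primary outcome.
- **Treatment of missing data.** A mixed model is already foreseen: "As an alternative statistical analysis method using linear mixed model ANOVAs or generalized estimating equation (GEE) for longitudinal analysis".

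**The concern.** Two stated rules fit together badly. An interaction of group with time captures a treatment effect when baseline is one of the times, because the groups start equal and then separate. Once baseline moves to the covariate side and only follow-up visits remain as outcomes, the treatment effect sits in the group main effect. The interaction then asks only whether that effect grows or shrinks between follow-up visits. A product that works by month 3 and keeps working produces no interaction, while one whose benefit is lost after supplementation stops produces a large one.

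The sample size formula, meanwhile, is for a third quantity: a two-group difference in mean follow-up, adjusted for baseline. If the analyst takes the interaction as the primary result, a lasting benefit could be reported as no effect. A significant interaction would not by itself say which product differs from placebo, or when.

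**Working it through.** **Inputs from the article.** Difference 0.60 SD; rho = 0.7; v = 1; w = 2; alpha 0.05 two-sided; power 0.80; 29 per arm before attrition and 40 after; three equal arms.

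**Assumptions added here.** Equal correlation 0.7 between all visits; both active arms 0.60 from placebo (one active arm alone gives the same interaction power); two fading patterns after month 6 (halved, or gone).

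**1. What the sample size formula targets.** R = [1 + (w − 1)rho]/w − v·rho²/[1 + (v − 1)rho] = 1.7/2 − 0.49 = 0.85 − 0.49 = 0.36. This is the variance factor of a baseline-adjusted mean of two follow-up visits, so the formula sizes a two-group main effect.

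The formula with these inputs gives n = 0.36 × [2(1.96 + 0.84)²/0.36 + 1.96²/4] = 0.36 × (43.56 + 0.96) = 16.0, hence 17 per group. The stated 29 is not reproduced. That is a separate matter; 29 is used below because it is the planned figure.

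**2. Power of the sized contrast at 29 per arm.** Standard error = √(2 × 0.36/29) = 0.158; 0.60/0.158 = 3.81. Power is about 96% (noncentral t; 97% by the normal approximation) at 0.05, and about 91% at 0.05/3. For month 6 alone the factor is 1 − 0.49 = 0.51 and power is about 88%.

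**3. Interaction with baseline as covariate only.** Noncentrality = n × (sum of squared interaction effects)/(1 − rho).

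- *Constant effect, two or four follow-up visits.* Each arm's profile is flat, so every interaction effect is 0 and the noncentrality is 0. Power equals alpha, 5%, at any n. Simulation at 29 per arm gives 0.052 (two visits) and 0.047 (four).
- *Effect gone after month 6, four visits.* The active profiles deviate from their own mean by ±0.3. After removing the visit means, the interaction effects are ±0.2 for placebo and ±0.1 for each active arm. Sum of squares = 4 × (0.04 + 0.01 + 0.01) = 0.24; noncentrality = 29 × 0.24/0.3 = 23.2; power 95 to 97% (simulation and noncentral F).
- *Effect halved after month 6, four visits.* Sum of squares = 0.24/4 = 0.06; noncentrality = 5.8; power 37 to 38%.

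**4. Interaction with baseline as a level of time, constant effect, 29 per arm.** The factor 2/3 below comes from two equal active arms against placebo: (2/3)² + 2 × (1/3)².

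- *Level only, three visits.* Profile (0, 0.6, 0.6) has centred sum of squares 0.24; × 2/3 = 0.16; noncentrality 29 × 0.16/0.3 = 15.5; power about 89%.
- *Level only, five visits.* Centred sum of squares 0.288; × 2/3 = 0.192; noncentrality 18.6; power about 87 to 88%.
- *Level and covariate together.* Simulated power is about 93% (three visits) and 91 to 92% (five visits), with type I error 0.045 to 0.052. The adjusted group difference at baseline is zero by construction, so the interaction picks up the follow-up differences.

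**5. Side by side (29 per arm).**

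| Test | Constant 0.60 | Halved after month 6 | Gone after month 6 |
|---|---|---|---|
| Sized contrast, mean of months 3 and 6 | 96% | 96% | 96% |
| Interaction, baseline covariate only, 4 follow-up visits | 5% | 37–38% | 95–97% |
| Interaction, baseline a time level | 87–93% | – | – |

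The sized contrast does not change across the row because it uses only on-treatment visits.

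**The case against.** The strongest reply is that the 5% belongs to one reading only. The article never says that baseline leaves the time factor, and if it stays in, with or without the covariate, the interaction has adequate power. That stands. A reader might infer that the primary test simply cannot detect the treatment effect; the text does not establish this.

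Three further inferences are tempting and should not be drawn.

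- *That the primary test is an 8-df test over five visits.* The Statistical analysis section names no visit set. A five-level time factor needs baseline as a level, whereas the 5% result needs it not to be one, so the two cannot describe the same model.
- *That double use of baseline breaks the compound-symmetry assumption and so the analysis.* The article uses that structure only when the assumption is met, and otherwise turns to multivariate or Huynh-Feldt methods.
- *That repeated measures ANOVA will discard incomplete participants.* The article plans multiple imputation, an intention-to-treat primary approach and mixed models or GEE on all available data.

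It is also fair that the interaction is called one primary component, not the only test: group differences and Bonferroni t tests run beside it. This softens the consequence but does not remove it, because no single comparison is made decisive. Exact model terms can be left to an analysis plan. Here, though, the article has itself stated the interaction, the baseline adjustment and the sized quantity, and these do not line up.

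**Conclusion.** The point holds in a conditional form. On the ordinary reading of a baseline-adjusted repeated measures model, the named interaction has 5% power against a constant 0.60 difference at any sample size. With four follow-up visits it does better the more of the benefit is lost after month 6: about 37% if halved and about 95% if gone, at 29 per arm. If baseline is a time level, power is about 87 to 93% for a constant effect, so the loss is a consequence of the reading and not certain.

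What does not depend on the reading is the mismatch of target. The interaction is a three-arm omnibus test, possibly including the off-supplement visits, and part of it can come from probiotic against synbiotic. It is neither the two-group baseline-adjusted mean difference that the sample size formula describes (about 96% power at 29 per arm) nor Aim 1's comparison with placebo.

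The figures rest on equal correlation of 0.7 at all visits, a 0.60 difference and the two illustrative fading patterns. The zero interaction under a constant effect needs none of these values.

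**What to change.** State in the Statistical analysis section that:

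1. the primary test for HOMA-IR is the baseline-adjusted active-minus-placebo difference over the on-treatment visits, that is the mean of months 3 and 6, matching w = 2, for each active product;
2. it is estimated from the linear mixed model already named under Treatment of missing data, with baseline HOMA-IR as covariate and follow-up visits as outcomes;
3. months 12 and 18 are secondary contrasts for persistence after supplementation;
4. the group-by-time interaction and the repeated measures ANOVA are supportive.

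The cost is wording only. The method is already in the article and no further data are needed. What is given up is the omnibus interaction as a primary result. Power has room for a multiplicity adjustment over the pairwise comparisons: about 91% at 0.05/3 with 29 per arm, on the article's own assumptions.

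### The only pairwise test named, a Bonferroni-adjusted t test at each visit, ignores baseline and does not match the baseline-adjusted contrast that the sample size assumes

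*Protocol article*

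**What the plan says.** The Protocol article's Sample size section sets a two-sided alpha of 0.05, "and statistical power of 1 − β = 0.80", and sizes the trial "for detecting a standardized effect size of at least Δ = 0.60". Its formula is a two-group contrast multiplied by a factor R, which takes credit for one pre-intervention measurement (v = 1), two post-intervention measurements (w = 2) and a correlation of 0.7. It makes no allowance for multiple comparisons. The section states 29 per group, raised to 40 for attrition.

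The Statistical analysis section makes repeated measures ANOVA the main approach, with the group-by-time interaction as the component of primary interest. It says the model permits inference on differences between treatment groups, and that baseline values are covariates in every fitted model. Alongside the ANOVA, an independent t "test along with Bonferroni adjustment will be conducted for comparing outcomes in each follow-up time point between study groups". The size of the Bonferroni family is not given. Biochemical assays lists four follow-ups: months 3, 6, 12 and 18.

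Aim 1 compares each product with placebo on insulin resistance, the primary outcome, among other measures. Aim 5 is "To compare the effects of probiotic and synbiotic supplements on gut microbiota, anthropometric, glycemic, and lipid profiles".

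**The concern.** With three arms, both the interaction and an overall group effect are omnibus tests. A significant result says that the arms differ somewhere, not where. Aims 1 and 5 are questions about pairs, and the article specifies no pairwise contrast from the model, so the t tests are the only stated route to those answers.

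The t test departs from the sample-size contrast in three ways: it uses no baseline, it uses one follow-up instead of the mean of two, and its alpha is smaller. It also sits badly with the statement that baseline is adjusted in all fitted models, because an independent t test has no covariates. Either the t tests ignore baseline, or that statement is meant to cover them and they are not t tests.

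At stake is the power to say which product works, although the trial already collects the baseline and repeated measurements that would supply it.

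**Working it through.** **Inputs (Sample size section).** Effect Δ = 0.60, alpha = 0.05 two-sided, power 0.80, v = 1, w = 2, ρ = 0.7, 29 per arm before the attrition allowance and 40 recruited. Assumption: Δ is standardised by the raw SD at a single visit.

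**1. The plan's own figure.**
R = [1 + (w − 1)ρ]/w − vρ²/[1 + (v − 1)ρ] = 1.7/2 − 0.49 = 0.36.
n = 0.36 × [2(1.96 + 0.84)²/0.36 + 1.96²/4] = 0.36 × (43.56 + 0.96) = 16.0.
The stated 29 is therefore not reproduced; the printed formula gives 16 to 17. That is a separate matter to reconcile. Below I use the numbers the trial plans, 29 and 40.

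**2. Effective effect size for each analysis.**
- Independent t test at one visit: variance factor 1, d = 0.60.
- Baseline-adjusted contrast at one visit: factor 1 − ρ² = 0.51, d = 0.60/√0.51 = 0.84.
- Baseline-adjusted mean of two follow-ups: factor R = 0.36, d = 0.60/0.60 = 1.00.

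**3. Power.** Noncentral t with 2n − 2 degrees of freedom and noncentrality d√(n/2). For the t test at n = 29 the noncentrality is 0.60 × √14.5 = 2.28. The critical value is 2.00 at alpha 0.05 and 2.47 at 0.05/3.

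| Analysis | n per arm | 0.05 | 0.05/3 | 0.05/6 | 0.05/12 |
|---|---|---|---|---|---|
| t test, one visit | 29 | 61% | 43% | 34% | 25% |
| t test, one visit | 40 | 76% | 60% | 49% | 40% |
| Baseline-adjusted, one visit | 29 | 88% | 77% | 68% | 59% |
| Baseline-adjusted, one visit | 40 | 96% | 90% | 85% | 79% |
| Baseline-adjusted, mean of two | 29 | 96% | 91% | 85% | 79% |
| Baseline-adjusted, mean of two | 40 | 99% | 98% | 96% | 93% |

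The divisor 3 is the three pairs within a visit. Twelve is three pairs by four visits, the largest family the design offers for one outcome. Six is an intermediate case.

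**4. Dependence on the correlation.** The t test figures do not involve ρ. The adjusted figures do. At ρ = 0.5 the two-visit factor is 0.75 − 0.25 = 0.50, so d = 0.60/√0.50 = 0.85, and three-pair power is about 77.5% at 29 per arm and 91% at 40. That is still well above the t test's 43% and 60%.

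**The case against.** The strongest reply is that the t tests are not the main analysis. Repeated measures ANOVA is, baseline is a covariate in every fitted model, and Treatment of missing data adds mixed models or GEE for comparing groups. This stands, and it limits the point: nothing here shows that the main analysis loses power. It does not remove the point, because no pairwise contrast from any of those models is specified. Nor is this merely detail left to an analysis plan, since the article itself names a pairwise test, and one that conflicts with its own baseline statement.

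A reader might infer three stronger things that the document does not support.
- *That the t tests have well under half the claimed power.* Half of 80% is 40%. The natural reading of the Bonferroni family, three pairs within a visit, gives 43% at 29 per arm and 60% at 40. Power falls clearly below 40% only at 29 completers with a larger family, which the protocol never states.
- *That 29 per arm is what to expect.* It is the case in which the attrition allowance is used up. The plan recruits 40 and intends to collect outcomes after discontinuation, so 40 is the other end of the range.
- *That running both analyses gives two equal routes to a positive claim.* The ANOVA is ranked as main and the t tests carry a correction, so this is weak.

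**Conclusion.** The mismatch holds: the one pairwise test named is not the contrast for which the trial was sized. At effect 0.60 its power lies below 80% at every point of the planned range, from 76% (40 per arm, no adjustment) to 43% (29 per arm, three pairs), and lower still if the Bonferroni family also spans visits. At the same three-pair alpha, the sample-size contrast would have about 91% at 29 per arm and 98% at 40. The t test figures rest on Δ applying to the raw single-visit SD; the adjusted figures also need ρ = 0.7 between baseline and the follow-ups and between the two follow-ups. The shortfall concerns the pairwise answers to Aims 1 and 5, not the overall ANOVA. The change is worth making because it costs almost nothing.

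**What to change.** Replace the independent t tests with baseline-adjusted pairwise contrasts from the primary repeated-measures model. Define the primary contrast as the mean of the two on-treatment follow-ups, months 3 and 6, and say that these are the w = 2 follow-ups of the sample size; the article does not identify them, so this is a reading to confirm. Apply Bonferroni or Holm once, over the three HOMA-IR pairs (probiotic versus placebo, synbiotic versus placebo, synbiotic versus probiotic). Report individual visits as secondary estimates with confidence intervals and no separate claim of success.

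If a single visit is preferred as primary, three-pair power is 77% at 29 per arm and 90% at 40, so the two-visit mean is the choice that keeps 80% at 29 when ρ = 0.7.

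The cost is analysis wording and one decision on the primary time summary, to be fixed before unblinding. No additional participants, visits or measurements are needed.
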